**Methods/Design:**

The study will enroll 600 patients with type 2 diabetes who have angiographically normal ventricular function and coronary arteries. The goal of the MASS IV-DM Trial is to achieve a long-term evaluation of the development of coronary atherosclerosis by using angiograms and coronary-artery calcium scan by electron-beam computed tomography at baseline and after 5 years of follow-up. In addition, the incidence of major cardiovascular events, the dysfunction of various organs involved in this disease, particularly microalbuminuria and renal function, will be analyzed through clinical evaluation. In addition, an effort will be made to investigate in depth the presence of major cardiovascular risk factors, especially the biochemical profile, metabolic syndrome inflammatory activity, oxidative stress, endothelial function, prothrombotic factors, and profibrinolytic and platelet activity. An evaluation will be made of the polymorphism as a determinant of disease and its possible role in the genesis of micro- and macrovascular damage.

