### Statistical analyses

All data will be expressed as means ± SD. Differences between the data of patients for clinical and biological characteristics and basal hemodynamic parameters were analyzed by the nonparametric Mann-Whitney test. Changes in hemodynamic parameters at baseline and the end of follow-up will be analyzed with the paired Student *t *test. Comparisons between coronary artery dimensions at baseline and the end of the study will be made by 2-way ANOVA with repeated measures for experimental condition factor followed by the Fisher protected least-significance difference test.

The Spearman test will be used to find the correlates of coronary endothelium-dependent vasoreactivity. Due to its skewed distribution, urinary albumin excretion rate will be log transformed in the correlation analyses. A backward linear multiple regression will be performed to find the independent predictors for endothelium-dependent coronary vasoreactivity. Statistical significance is assumed when P < 0.05.

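### The vasoreactivity regression selects predictors by backward elimination at a flat P < 0.05, and the log transform of albumin excretion is assigned to a rank correlation, where it has no effect

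*Protocol article*

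**What the plan says.** All the rules at issue stand in the Statistical analyses section of the protocol article.

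- Selection: "A backward linear multiple regression will be performed to find the independent predictors for endothelium-dependent coronary vasoreactivity".
- Threshold: "Statistical significance is assumed when P < 0.05". The sentence carries no exception or adjustment.
- Correlation: "The Spearman test will be used to find the correlates of coronary endothelium-dependent vasoreactivity". No other correlation method is named.
- Skewness: "Due to its skewed distribution, urinary albumin excretion rate will be log transformed in the correlation analyses".
- Description: "All data will be expressed as means ± SD".
- The only device in the section related to multiplicity applies to coronary artery dimensions: "2-way ANOVA with repeated measures for experimental condition factor followed by the Fisher protected least-significance difference test".

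The candidate predictors are neither listed nor counted. Laboratory measurements details eight quantities: HbA1c, total cholesterol, HDL, triglycerides, creatinine, urinary albumin excretion, and calculated LDL and creatinine clearance. The abstract names wider domains to be investigated: "metabolic syndrome inflammatory activity, oxidative stress, endothelial function, prothrombotic factors, and profibrinolytic and platelet activity".

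**The concern.** Backward elimination uses the data to decide which variables stay, and the flat threshold then reads the survivors as if the model had been fixed in advance. With several candidates, some noise variables will pass by chance and be reported as independent predictors. The Background section says the study aims to identify a protective mechanism. This regression is the only multivariable procedure named, so readers are likely to take its list of survivors as part of the answer.

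The skewness rule is a separate fault. The section recognises that albumin excretion is skewed, but corrects it in the one place where the correction can do nothing. The next sentence introduces a linear model, where the scale of a predictor does affect fit and leverage, and no transform is stated there. The rule on means ± SD conflicts with the same recognition of skewness.

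**Working it through.** **Inputs.** The threshold is 0.05 (Statistical analyses); its sidedness is not stated, and two-sided t tests are assumed. The sample size is 600: "The study will enroll 600 patients with type 2 diabetes". The number of candidates, k, is not stated. The assumed range is k = 8 (the quantities in Laboratory measurements) to k = 50, with 20 and 30 between. Every candidate is assumed null. The article gives no error rate for this analysis, so there is no figure to reproduce.

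**1. Multiple testing alone.** For k independent null tests at 0.05, the expected number of false positives is 0.05k, and the chance of at least one is 1 − 0.95^k.

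**2. Backward elimination, simulated.** Each setting used 1,000 datasets of n = 600 with normal noise predictors. The variable with the largest P value was removed until all remaining had P < 0.05. Pairwise correlation between predictors was 0 or 0.3. The Monte Carlo standard error near 64% is √(0.64 × 0.36 / 1000) ≈ 1.5 points.

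| k | Expected false, 0.05k | At least one, 1 − 0.95^k | Simulated, correlation 0: at least one (mean kept) | Simulated, correlation 0.3: at least one (mean kept) |
|---|---|---|---|---|
| 8 | 0.40 | 33.7% | 32.9% (0.40) | 32.6% (0.44) |
| 20 | 1.0 | 64.2% | 61.4% (0.99) | 66.9% (1.19) |
| 30 | 1.5 | 78.5% | 78.8% (1.59) | 82.4% (1.80) |
| 50 | 2.5 | 92.3% | 92.9% (2.64) | 94.6% (3.12) |

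**3. What selection adds.** With uncorrelated candidates, the simulated rate differs from the formula by −2.8 to +0.6 points, which is little more than simulation error. With correlation 0.3, it differs by −1.1 to +3.9 points. The formula treats tests as independent, so that second comparison is approximate. The mean number kept shows the effect more clearly: at correlation 0.3 and k = 50 it is 3.12 against 2.5, about 25% more. Most of the false-positive rate is therefore multiplicity, and a full 20-variable model read at P < 0.05 would give about 64% as well.

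**4. P values after selection.** A valid P value for a null variable falls below 0.05 one time in twenty. Every variable left by this procedure has P < 0.05, because that is the condition for staying. Its printed P value therefore cannot be read at face value.

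**5. The log transform.** A log is strictly increasing, so ranks are unchanged, and so are Spearman's rho and its P value. As an illustration, take a log-normal marker (log SD 1.5, n = 600) and an outcome equal to 0.1 times the logged marker plus standard normal noise:

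- Spearman: 0.0559 (P = 0.171) raw, and 0.0559 (P = 0.171) logged.
- Pearson: 0.042 raw, 0.069 logged.

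The Pearson contrast depends on a relation built to be linear on the log scale. It shows only that scale can matter in a linear analysis.

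**6. Description.** One sentence of the section applies means ± SD to all data, and another calls albumin excretion skewed. The study also records data that a mean cannot describe, such as the three-category angiographic rating in the Patients section.

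**The case against.** The strongest reply is that the candidate set is not in the document. A reader might infer that dozens of biomarkers and gene loci all enter this regression. The article does not support that: the abstract lists domains to investigate, not covariates, and Genetic Analysis ties the loci to coronary disease progression, not to vasoreactivity. This stands, and it is why the result is given as a range starting at 8.

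A second reply is that multiplicity rules and candidate lists often sit in an analysis plan or full protocol that is not shown. This also stands. The absence of an adjustment is not the finding; the finding is the selection rule and threshold that the article does fix.

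Third, the all-null assumption is a worst case, since the Background lists established risk factors. That lowers the expected number of false entries among real ones, but it does not make post-selection P values valid.

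Fourth, a reader might take the log as the plan's only protection against skewness. It is not: Mann-Whitney and Spearman are rank methods and tolerate skewed data. The log before Spearman is redundant and harms no result. Linear regression does not require normally distributed predictors, and the phrase about correlation analyses may have been meant loosely to include the regression. If so, the text should say so.

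Finally, this is an observational cohort that its Final Considerations present as leading to more specific studies, so strict error control is partly a matter of judgement. That argues for an exploratory label. It does not defend calling the survivors independent predictors at P < 0.05.

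**Conclusion.** The point holds for what the Statistical analyses section fixes. Backward elimination with a flat P < 0.05 gives invalid P values for the vasoreactivity predictors. The chance of at least one false predictor is about one in three with 8 null candidates, 61-67% with 20 and 93-95% with 50. These figures assume that all candidates are null, that n = 600, and that pairwise correlation is 0 to 0.3; k = 20 and above is an assumption. The main cause is multiple testing, with a small addition from selection. How far retained coefficients would be exaggerated was not calculated, and no figure is claimed.

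The log step is inert where it is placed and unstated where it could matter. The rule on means ± SD conflicts with the section's own description of albumin excretion.

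It would go too far to say that the study's whole output will be false. The regression covers one outcome, and the article's aims also include events and disease progression, for which no backward selection is stated.

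**What to change.** 1. Replace backward elimination with a prespecified full linear model whose number of terms is limited by the sample size, or with a penalised model and bootstrap optimism correction.
2. Apply Benjamini-Hochberg false-discovery control at 5% across the candidate predictors of the prespecified model, and label the results exploratory. Dropping the selection alone is not enough, because multiplicity drives most of the error. As a benchmark, a per-variable threshold of 0.05/k gives 1 − (1 − 0.05/k)^k ≈ 4.9% for at least one false predictor, and 4.0-5.6% when simulated with backward elimination for k = 8 to 50. Benjamini-Hochberg is less strict than this when some candidates are real.
3. Enter log albumin excretion in the linear regression and drop the log from the Spearman step.
4. Report skewed variables as median (IQR) and categorical ones as n (%), keeping means ± SD for roughly symmetric measurements.

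The cost is a change of wording and standard software, with no new data or visits. The downside is fewer nominally significant predictors.

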## Discussion

The MASS IV-DM trial is a study designed to include diabetic patients with suspected myocardial ischemia whose conventional angiogram showed coronary arteries to be angiographically normal.

Even if diabetes has been implicated as the main causal factor in the development of coronary atherosclerosis, the question that arises is what are the protective mechanisms of this so-called micro- and macrovascular disease. On the other hand, the mechanisms associated with coronary artery disease are likely multifactorial, including hypertension, abdominal obesity, and plurimetabolic syndrome; diabetes plays an important role in this scenario.

Patients with CAD without diabetes compared with diabetic patients have coronary atherosclerosis that is more advanced, and rates of ventricular dysfunction and cardiac events are higher. Additionally, the prognosis of CAD is less favorable in patients with diabetes than their nondiabetic counterparts; mortality after infarction is higher in diabetic patients and is particularly high among women.

Few studies discuss in depth the occurrence of major cardiovascular events in long-term follow-up in patients with type 2 diabetes with angiographically normal coronary arteries.

The MASS IV-DM Trial is a great opportunity to address all these issues, and it will add relevant information to this field.

### Ethical Considerations

The MASS IV-DM Trial is conducted in accordance with the principles of the Declaration of Helsinki and with laws and regulations of our country. The Ethics Committee of the Heart Institute of the University of São Paulo, Brazil approved the study protocol. The attending physician obtained written informed consent from the study participants.

### Final Considerations

The MASS IV-DM trial is designed to include diabetic patients with clinically suspected myocardial ischemia in whom conventional angiography shows angiographically normal coronary arteries. The idea that diabetes mellitus is a micro- and macrovascular disease leads us to reflect on the difficulties of comprehending the pathophysiological mechanisms of the disease. The question that arises is what is the protective mechanism of vascular involvement? The result of extensive research including angiographic follow-up by several methods, vascular reactivity, pro-thrombotic mechanisms, genetic and biochemical studies may facilitate this understanding and lead to more specific studies for the prevention of so-called micro- and macrovascular disease.

## Abbreviations

MASS IV: Medical Angiplasty or Surgery Study; DM: Diabetes Melittus; LDL low-density lipoprotein cholesterol; VLDL: high triglycerides, increased; CAD: coronary artery disease; AMI: acute myocardial infarction; PCI: Percutaneous Coronary Intervention; CABG: Coronary Artery Bypass Graft; NCEP: National Cholesterol Education Program; CT: Computed tomography; MPI = Stress myocardial perfusion imaging; CAC: CAC-Scan = Coronary-artery calcium scan; EBCT: electron-beam computed tomography; SPECT: Single Photon Emission Computed Tomography; MBq Mega Becquerel; Tc: technetium; RAO: Right anterior oblique; LPO: Left posterior oblique; keV: Kilo eletrovolts; ESS: exercise score summed; RSS: resting score summed; DSS: difference in the score summed; mHz: mili hertz; TRIVE: relaxation time of the left ventricle; HbA1c: haemoglobin A1C; DNA: Deoxyribonucleic acid
